#### Data collection and management

Outcome measures will be collected at one-week before intervention, one-week post-intervention and four-weeks post-intervention (Fig. 2).

**Figure 2 fig-2:**
[figure not shown]
Flow diagram of the planned protocol pathway.

### Data analysis

#### Statistical approach

The analysis of the data will be blinded, as each subject and condition will be coded by a consultant who will not be involved in the investigation. SPSS software version 25.0 will be used for all analyzes (SPSS Inc. Armonk, NY, USA). Data will be reported as mean with SD or median with interquartile range. Statistical analyzes were performed on an intention-to-treat basis, with imputation of missing data using the average of the remaining participants.

Normality tests will be performed using the Shapiro–Wilk test given the number of subjects needed for each group. In addition, the homogeneity of variance and the sphericity of the data will be determined. In the case of not assuming any of these assumptions, the Green-Hausser correction will be used for the interpretation of subsequent analyzes. A three-way repeated measures ANOVA will be conducted to analyze both primary and secondary outcomes. The factors considered in this analysis will include time and intervention. Additionally, the third factor will encompass variables such as employment status, education level, or income. In case of significant interaction, a two-way repeated measures ANOVA (time (pre-post) × intervention (in-group PNE, individually PNE, no intervention)) will be performed for each employment status (employed or unemployed). Furthermore, a two-way repeated measures ANOVA (time (pre-post) × intervention (in-group PNE, individually PNE, no intervention)) will be performed for each educational level (high or low). Lastly, a two-way repeated measures ANOVA (time (pre-post) × intervention (in-group PNE, individually PNE, no intervention)) will be performed for income (≤USD 545, or >USD 545). If interactions are detected in any of the 2-way ANOVAs, a *post-hoc* analysis will be conducted using multiple pairwise comparisons employing a *t*-test corrected by Bonferroni. The significance level will be set at 5%.

A stepwise multiple linear regression will be performed to estimate the influence of changes in primary and secondary outcomes. In each model, adjustments will be made for employment status, educational level, and income. In this analysis, the aforementioned variables will be sequentially incorporated into each model.

The calculation of Cohen’s d will be performed to determine the effect size (ES) of all intragroup variables. Consider a small effect size if it is less than or equal to 0.2; medium of 0.3 to 0.5 and large of 0.5 to 0.8 (Jacob, 1992).

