#### Sample size

Sample size calculation was performed with G*Power 3.1. A repeated measures analysis of variance (ANOVA) model with within-between interaction, was used. Assuming an alpha risk of 0.05, a power of 0.95, a correlation between repeated measures of 0.5, a 10% drop-out rate, and a small effect size (0.26), a total of 20 participants per group (three groups) were required. The effect size estimate was based on a previous study about education compared to physical therapy for the FABQ outcome (Marshall et al., 2022) and the recommended effect size for clinical studies (Lakens, 2013).

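### Filling missing outcomes with the mean of the observed participants either understates the standard error or dilutes the treatment difference, so the intention-to-treat inference is not valid

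*Protocol article*

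**What the plan says.** The Statistical approach section of the protocol article sets the analysis set and the missing-data rule in one sentence: "Statistical analyzes were performed on an intention-to-treat basis", "with imputation of missing data using the average of the remaining participants". The filled data then go into the main model: "A three-way repeated measures ANOVA will be conducted to analyze both primary and secondary outcomes". Where an interaction is found, the follow-up is "multiple pairwise comparisons employing a *t*-test corrected by Bonferroni".

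The Sample size section shows that the rule will be used, because it plans for losses: "Assuming an alpha risk of 0.05, a power of 0.95, a correlation between repeated measures of 0.5, a 10% drop-out rate".

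The article does not say whether the mean is taken within the participant's arm or across all arms. It names no mixed model, multiple imputation or sensitivity analysis.

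**The concern.** Mean filling gives every participant with a missing outcome the same value. It ignores that participant's own baseline, although the sample size calculation assumes a correlation of 0.5 between measurements, and it carries no uncertainty about the filled value.

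- **Own-arm mean.** The point estimate is unchanged if data are missing completely at random. However, participants who were not measured are counted as measured, so the standard error is too small and the tests reject too often.
- **All-arm mean.** Each filled value is the same in every arm, so each one pulls the arms together and the difference shrinks towards zero.

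The two readings err in different ways, and the choice between them is left open until the data are in hand. The second objective is also exposed: a mean that ignores employment, education and income blurs the interactions that the three-way ANOVA is meant to test. The planned within-group Cohen's d suffers too, because mean filling shrinks the SD at the filled visit.

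**Working it through.** **Inputs from the article.** Alpha 0.05, correlation 0.5, drop-out 10%, three arms, three measurement times, effect size 0.26, 20 per group (Sample size; Data collection and management). The Abstract gives 69 in total, i.e. 69/3 = 23 per arm, and also 33 per arm. These sizes conflict, so 20, 23 and 33 are all used below.

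**Assumptions.** SD = 1, post-treatment values missing completely at random, true differences of 0.5 or 0.70 SD. Missing rates above 10% are scenarios and are not in the article.

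**The plan's own figure.** For the within-between interaction, λ = f²·N·m/(1−ρ), df1 = (k−1)(m−1), df2 = (N−k)(m−1). With f = 0.26 (read as Cohen's f), k = 3, m = 3 and N = 51, λ = 0.0676 × 51 × 3/0.5 = 20.7 on 4 and 96 df, and power is 0.961. Then 51/0.9 = 56.7, rounded up to 57, or 19 per group against the stated 20. With f = 0.25, N = 54 and 54/0.9 = 60, exactly 20 per group. So the stated size is close to reproducible, and 10% loss is built into it.

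**Own-arm mean, change from baseline, n = 23.** Let p be the fraction missing. With ρ = 0.5 the arm mean of change has true variance 1/n_obs + 1/n − 2ρ/n = 1/n_obs. The change score of a filled participant still varies through baseline (variance 1), so the sample variance stays near 1 and the reported variance is 1/n. The ratio of reported to true SE is therefore √(n_obs/n) = √(1−p).

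At 20% missing:
- reported SE: √(2/23) = 0.295 (simulated 0.293)
- true SE: √(2/18.4) = 0.330 (simulated 0.33)

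The reported value is what complete data would give, as if nobody had dropped out. The type I error of a two-sided 5% t-test on 44 df is P(|t| > 2.015·√(1−p)).

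| Missing | SE ratio | Type I, formula | Type I, simulated |
|---|---|---|---|
| 10% | 0.949 | 6.2% | 6.4–6.6% |
| 20% | 0.894 | 7.8% | 7.4–8.1% |
| 30% | 0.837 | 9.9% | 9.7–10.2% |

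**Own-arm mean, post-treatment values.** Here the filled values also shrink the sample variance. The SE ratio is √[(n_obs−1)/(n−1) × n_obs/n].

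| n per arm (missing) | SE ratio | Pairwise type I, simulated | Time-by-group F test, simulated |
|---|---|---|---|
| 20 (2) | √(17/19 × 18/20) = 0.897 | 7.5% | 6.7% |
| 33 (3) | √(29/32 × 30/33) = 0.908 | 7.4% | 6.5% |
| 20 (4) | √(15/19 × 16/20) = 0.795 | 11.9% | 8.5% |
| 33 (7) | √(25/32 × 26/33) = 0.785 | 12.4% | 9.4% |

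**All-arm mean.** The difference is multiplied by n_obs/n.
- A true 0.70 SD becomes 0.63, 0.56 and 0.49 SD at 10%, 20% and 30% missing (0.70 × 0.9, × 0.8, × 0.7). Simulation agrees.
- A true 0.5 SD is estimated at 0.45 with 2 of 20 or 3 of 33 missing, and at about 0.40 with 4 of 20 or 7 of 33.
- Type I error stays near 5%.
- F-test power for 0.5 SD at n = 33 with 3 missing is 0.45, against 0.49 when only observed data are used.
- Change-score power for 0.70 SD at n = 23 with 20% missing is about 45%, against 54% with observed data only and 64% with complete data.

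**Without mean filling.** Analysing only observed values under the same assumptions recovers the true difference (0.50 for 0.5 SD). At n = 33 with 3 missing per arm, the reported SE matches the true one (0.257 against 0.256), pairwise type I error is 4.9% and the F test 5.0%.

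**The case against.** The strongest reply is about size. Only 10% loss is planned, and at 10% the distortion is moderate: type I error of about 6.5% to 7.5%, or a tenth off the effect. The larger figures belong to missing rates that the article does not predict. This stands.

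The power comparison also needs care. At 20% missing, the fall from 64% to about 45% is not all due to the rule. Observed data alone give 54%, so mean filling accounts for about 9 points (54 − 45). At 10% it accounts for about 5 (59% against 54%).

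The size depends on the test. The change-score t-test gives the mildest inflation at about 20% missing and the post-value t-test the strongest, with the F test between them or close to the change-score result. The pairwise figures are for uncorrected tests, whereas the plan applies Bonferroni correction and only after an interaction. The corrected threshold would rest on the same understated SE.

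Finally, all randomised participants do stay in their allocated arms. The fault is in the inference made under the intention-to-treat label, not in exclusions. Under data missing completely at random, each reading also gets one thing right: the own-arm mean leaves the estimate unbiased, and the all-arm mean keeps the type I error.

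None of this rescues the rule. It is a method that the article specifies, not detail left to an analysis plan, and neither reading gives both a correct estimate and a correct standard error.

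**Conclusion.** The concern holds: the rule is wrong as written. At the planned 10% loss, the own-arm reading makes the standard error 5% (change scores) to 10% (post-treatment values) too small. The all-arm reading makes the difference 10% too small. At about 20% loss the figures are roughly 11% to 22% on the standard error, or about 20% on the difference.

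These results assume a correlation of 0.5 and data missing completely at random, which is the most favourable case. Drop-out related to baseline or outcome would add bias that is not quantified here. The relative errors hardly depend on which of the conflicting sample sizes applies. The rule reaches every primary and secondary test and can be corrected at almost no cost, so it should be changed before any data are analysed.

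**What to change.** Replace the imputation clause with wording such as: *All randomised participants are analysed in their allocated arm with a likelihood-based linear mixed model that uses all observed visits; missing values are not singly imputed.*

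If the ANOVA is to be kept, use multiple imputation carried out separately by arm, with baseline score, employment status, educational level and income in the imputation model, and combine the results so that the imputation uncertainty enters the standard errors.

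One sensitivity analysis that shifts the imputed values of drop-outs would show how far the conclusion depends on the missing-at-random assumption. Its detail can sit in the analysis plan.

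The cost is a change of analysis wording. The planned software can fit mixed models and run multiple imputation, and sample size, visits and data collection stay as they are. Compared with own-arm mean filling, confidence intervals will be somewhat wider, because they will reflect the data actually observed.

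### The pre-intervention score enters the analysis only as a level of time; adding it as a covariate would tighten every between-arm comparison at almost no cost

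*Protocol article*

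**What the plan says.** All references are to the protocol article.

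- **Visits** (Data collection and management): the schedule reads "Outcome measures will be collected at one-week before intervention, one-week post-intervention and four-weeks post-intervention". Every outcome, including the primary one (FABQ), therefore has a baseline value.
- **Model** (Statistical approach): "A three-way repeated measures ANOVA will be conducted to analyze both primary and secondary outcomes. The factors considered in this analysis will include time and" (the next factor named is the treatment arm). The third factor is employment status, education level or income. If the interaction is significant, the follow-up models within levels of the social determinant are two-way ANOVAs of "time (pre-post) × intervention (in-group PNE, individually PNE, no intervention"), followed by Bonferroni-corrected pairwise t-tests.
- **Covariates** (same section): the stepwise regression adjusts for employment, education and income. The baseline value of the outcome is not named there or elsewhere.
- **Sample size**: a repeated measures ANOVA with within-between interaction. The error rate and power are given as "Assuming an alpha risk of 0.05, a power of 0.95", the correlation as "a correlation between repeated measures of 0.5", the expected loss as "a 10% drop-out rate" and the effect as "a small effect size (0.26"). These lead to 20 participants per group.

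**The concern.** In a repeated measures ANOVA the baseline score is part of the response. With two levels of time, the time × arm test is algebraically a one-way ANOVA of change scores. A change score subtracts the whole baseline (slope 1), whereas the slope of follow-up on baseline with equal variances is rho, which the plan sets at 0.5. Under randomisation the arms have equal expected baseline means, so the excess subtraction only adds noise.

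This matters because the hypothesis in the Introduction is that in-group education is superior to individual education. These are two active arms with the same content and the same therapist. That pairwise contrast is the one most short of precision, and the article's figures put only 20 to 33 participants in each arm.

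**Working it through.** **Inputs.** From Sample size: alpha 0.05, power 0.95, rho = 0.5, effect size 0.26 (read as Cohen's f, the G*Power input for this test), 10% drop-out, 20 per group. From the Abstract: 69 in total (69/3 = 23 per arm) and also 33 per arm. All three arm sizes are carried through.

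**1. The plan's own figure.** Noncentral F with lambda = f²·N·m/(1−rho), df1 = 2(m−1), df2 = (N−3)(m−1), where m is the number of time levels.
- m = 3: 51 in total, 17 per group; 17/0.9 gives 19 per group, close to the stated 20.
- m = 2: 63 in total, 21 per group; 21/0.9 gives 24 per group. With 60 analysed, power is 0.949.

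The stated size is thus approximately reproduced, for the planned type of test, with the three visits.

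**2. Variance of a between-arm contrast at one follow-up visit** (per participant, in units of the score variance, equal SDs).
- Change score: 2(1−rho) = 2 × 0.5 = 1.00.
- Baseline-adjusted (ANCOVA): 1−rho² = 1−0.25 = 0.75.
- Ratio: 2(1−rho)/(1−rho²) = 2/(1+rho) = 1.33.
- SE ratio: √0.75 = 0.87, so the adjusted SE is about 13% smaller.

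| rho | change score | adjusted | ratio |
|---|---|---|---|
| 0.3 | 1.40 | 0.91 | 1.54 |
| 0.5 | 1.00 | 0.75 | 1.33 |
| 0.7 | 0.60 | 0.51 | 1.18 |
| 0.8 | 0.40 | 0.36 | 1.11 |

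These are large-sample values. In a simulation of 20,000 trials at rho = 0.5, with the slope estimated, the ratio was 1.31 at 20 per arm (0.1006/0.0767) and 1.32 at 33 per arm (0.0609/0.0462).

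**3. Where chance imbalance fits.** The gap between the two variances is 2(1−rho) − (1−rho²) = (1−rho)², which is 0.25 at rho = 0.5. That is exactly the variance contributed by the over-subtracted part of the baseline. Sensitivity to chance baseline imbalance is therefore already counted in the ratio.

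**4. In-group versus individual.** With m = 2 and rho = 0.5, lambda = 0.26² × N × 2/0.5 = 0.2704·N. The change-score variance is 1.00, so the SD of the arm mean changes is √0.2704 = 0.52. Assume three equally spaced arms with step d. Then d·√(2/3) = 0.52, so d = 0.64 SD. Two-sided noncentral t at alpha 0.05/3:

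| n per arm | change score | adjusted |
|---|---|---|
| 20 | 0.32 | 0.44 |
| 23 | 0.38 | 0.51 |
| 33 | 0.55 | 0.70 |

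With the same 0.64 SD and n = 20, the rise is from about 0.23 to 0.36 at rho 0.3, and from 0.54 to 0.63 at rho 0.7.

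**5. Omnibus test.** With two time levels, power goes from 0.924 to 0.977 at N = 54 (60 less 10%) and from 0.949 to 0.987 at N = 60. With three time levels the planned test already has 0.971 and 0.984, so there is little left to gain.

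**The case against.** The best case for leaving the plan alone is that design and analysis agree. Under randomisation the time × intervention test is unbiased, and the trial was sized for that family of test. This stands. A reader might infer that the planned analysis is invalid, or that 20 per group is wrong on this account; the article supports neither.

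Several limits on size also stand.
- The change-score identity needs two time levels. The article writes pre-post only for the follow-up two-way ANOVAs, while three visits are planned. The ratio in step 2 therefore belongs to a contrast at one follow-up visit and not to the whole three-way model.
- The correlation of 0.5 is a planning input. The test-retest coefficients quoted under the outcomes (0.966 for FABQ, 0.86 for PSEQ, 0.92 for NRS) are reliabilities and do not fix the trial's correlation. They do make higher values plausible, and the gain then shrinks, to a ratio of 1.11 at 0.8.
- A reader might count chance baseline imbalance as a second harm or as a bias. Step 3 shows that it is the same loss, and over repeated randomisation there is no bias.
- The pairwise power figures rest on equal spacing of the arms, which the article does not state.

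It can also be said that an article may leave covariates to a fuller document. That carries less weight here, because the article does fix the model and its factors and lists the adjustment variables.

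**Conclusion.** The point holds as a gain in precision that the plan forgoes. The article fixes a model in which the baseline score is only a level of time, and the adjusted model is more precise in large samples at every correlation below 1. At the plan's rho of 0.5, the unadjusted contrast at one follow-up visit has one-third more variance (about 1.31 times at 20 per arm). Over rho from 0.3 to 0.8 the excess runs from 54% down to 11%. For the comparison that the hypothesis is about, this means roughly 12 to 15 points of power at rho 0.5, given f = 0.26, equally spaced arms and Bonferroni correction. The three-arm omnibus test gains little. The change is worth making because it needs no new data, but nothing in the planned test is wrong without it.

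**What to change.** For FABQ and each secondary outcome, replace the time × intervention analysis with a model of the post-intervention scores at one and four weeks. Include arm, visit, arm × visit and the participant's own baseline score of that outcome. This is ANCOVA if a single visit is analysed, or a linear mixed model with unstructured covariance for both visits. Keep the social determinant and its interaction with arm as planned. Take the in-group versus individual contrast and its confidence interval from this model.

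Cost: a wording change in the Statistical approach section, one degree of freedom, and the assumption of a common linear baseline slope across arms. No extra visits, data or participants are needed, and the named software fits both forms. The change should be written down before any unblinded analysis.

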**Methods:**

A three-arm randomized controlled trial will be conducted. Sixty-nine participants with CLBP will be recruited in a 1:1:1 ratio. Participants, assessor, and statistician will be blinded to group assignment. The PNE intervention will be adapted to the context of the participants. An experimental group (*n* = 33) will receive PNE in an in-group modality, the other experimental group (*n* = 33) will receive PNE in an individually modality and the control group (*n* = 33) will continue with usual care. Additionally, participants will be encouraged to stay active by walking for 20–30 min 3–5 times per week and will be taught an exercise to improve transversus abdominis activation (bracing or abdominal following). The outcome measures will be fear avoidance and beliefs, pressure pain threshold, pain self-efficacy, catastrophizing, pain intensity, and treatment expectation. Outcome measures will be collected at one-week before intervention, immediately post-intervention, and four-weeks post-intervention.

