In chronic pain rehabilitation, it is essential to address the factors mentioned above (McCracken, 2005). In this sense, the biomedical approach to education may promote the fear-avoidance model (Louw et al., 2011), while the pain neuroscience education (PNE) promotes patients’ understanding of chronic pain and changes maladaptive thoughts and cognitions (Moseley, 2002; Meeus et al., 2010) with a biopsychosocial approach limiting the fear-avoidance model (Louw et al., 2016b). PNE has shown positive results on the kinesiophobia, catastrophizing, pain intensity, disability, and physical performance in patients with CLBP (Moseley, Nicholas & Hodges, 2004; Ryan et al., 2010; Louw et al., 2011; Malfliet et al., 2017; Rufa, Beissner & Dolphin, 2018; Núñez Cortés et al., 2023a; Nuñez Cortés et al., 2023b). A recent meta-analysis has shown that the in-group PNE had better results than individual PNE for kinesiophobia (Romm et al., 2021), and it has been identified, in other types of health education, that there are greater benefits in those people who received the in-group intervention (Riemsma, Taal & Rasker, 2003), probably supported by the fact that educational sessions conducted in-group modality can facilitate learning through social observation of positive behaviors exhibited by other members within the group (Romm et al., 2021; Salazar-Méndez et al., 2024). However, there are no primary studies comparing the two PNE modalities directly. On the other hand, despite increasing evidence that SDH are influential factors in clinical health outcomes to a greater extent than the quality and availability of medical care (Daniel, Bornstein & Kane, 2018), there are no studies that analyze specifically the influence of SDH factors (*e.g.*, educational level) on the effectiveness of PNE (Salazar-Méndez et al., 2024).

We hypothesize that there will be significant differences in favor of the intervention in-group modality compared to the individual modality. Furthermore, the effects will be influenced by the social determinants of health in both experimental groups.

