### Primary outcomes

#### Fear avoidance and beliefs

This variable will be evaluated with the Fear Avoidance Beliefs Questionnaire (FABQ). The FABQ presents a minimum detectable change of 5.4 for the physical activity subscale and 6.8 for the work subscale (George, Valencia & Beneciuk, 2010). The minimal clinically important change (MCID) is 4 points for the FABQ-Physical Activity scale (FABQ-PA) and 7 points for the FABQ-Work scale (FABQ-W) (Monticone et al., 2020). Its Spanish version has been validated with a high internal consistency (Cronbach *α* = 0.933) with good test-retest reliability (ICC = 0.966) (Kovacs et al., 2006). Higher scores indicate higher levels of fear avoidance beliefs (George, Valencia & Beneciuk, 2010).

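### Objective 2 rests on at least 18 interaction tests, each at 5%, and the only stated correction does not reach them

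*Protocol article*

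**What the plan says.** The Introduction states the second hypothesis outright: "Furthermore, the effects will be influenced by the social determinants of health in both experimental groups". Study objectives makes the influence of social determinants objective 2. Neither place calls it exploratory.

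The Statistical approach section sets out the test:

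- **Outcomes:** "A three-way repeated measures ANOVA will be conducted to analyze both primary and secondary outcomes".
- **Determinants:** besides time and intervention, "Additionally, the third factor will encompass variables such as employment status, education level, or income".
- **Threshold:** "The significance level will be set at 5" per cent, with no distinction between outcomes, determinants or steps.
- **Next step:** "In case of significant interaction, a two-way repeated measures ANOVA" is run within the levels of each determinant.
- **Correction:** only after an interaction in one of those two-way models, when a post-hoc "analysis will be conducted using multiple pairwise comparisons employing a *t*-test corrected by Bonferroni".

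The Abstract counts the outcomes: "The outcome measures will be fear avoidance and beliefs, pressure pain threshold, pain self-efficacy, catastrophizing, pain intensity, and treatment expectation". The FABQ is the only one under Primary outcomes, and it is described by two subscales: "The minimal clinically important change (MCID) is 4 points for the FABQ-Physical Activity scale (FABQ-PA) and 7 points for the FABQ-Work scale (FABQ-W"). Neither subscale is chosen as the primary score.

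**The concern.** The claim that a determinant changes the effect of pain neuroscience education (PNE) rests on the three-way interaction. That test is repeated over outcomes and determinants at an unadjusted 5%. No outcome or determinant is named as the one that decides hypothesis 2, and the words introducing the determinants leave their list open.

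The Bonferroni step does not protect this claim. It follows the interaction test, and it compares arms rather than determinant levels. If PNE works equally well at every level, a corrected arm comparison within one level can still be significant, although nothing is modified.

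At stake is one of the trial's two objectives. The Discussion expects the results to show how social determinants influence the effects and to guide how PNE is implemented. A chance interaction could be read as a finding about who benefits.

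**Working it through.** **The plan's own figure.** The document states no family-wise error rate for objective 2, so there is none to reproduce. The Sample size section does not bear on the point, because the error rate of each test does not depend on the number of participants.

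**Inputs from the Protocol article**

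- Outcomes: 6 (Abstract, Methods), all entering the three-way ANOVA (Statistical approach).
- Determinants: 3 named (Statistical approach).
- Level per test: 0.05 (Statistical approach).

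**Count.** 6 × 3 = 18 three-way tests. This is a floor:

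- Two FABQ subscales (Fear avoidance and beliefs) and two pain ratings, at rest and in activity (Pain intensity), make 8 scores: 8 × 3 = 24 tests.
- Counting also the three algometry sites on both sides (Algometry) replaces 1 score by 6: 8 − 1 + 6 = 13 scores, and 13 × 3 = 39 tests.

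The article describes these measurements separately but does not say that each is analysed separately, so 18 is the count to rely on.

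**Independent tests.** P(at least one significant) = 1 − 0.95^n.

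| Tests | Calculation | Result |
|---|---|---|
| 18 | 1 − 0.95^18 | 60.3% |
| 24 | 1 − 0.95^24 | 70.8% |
| 39 | 1 − 0.95^39 | 86.5% |
| FABQ as one score, 3 | 1 − 0.95^3 | 14.3% |
| FABQ as two subscales, 6 | 1 − 0.95^6 | 26.5% |

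The expected number of false positives among 18 tests is 18 × 0.05 = 0.9.

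**Correlated tests.** The document gives no correlation between outcomes or between determinants, so these values are assumptions. Data without any effect were simulated for three arms and three time points, with each binary determinant split 50/50 and 3,000 runs per setting. The table shows the chance of at least one significant three-way F test.

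| Correlation of outcomes / determinants (latent scale) | 18 tests | 24 tests | 39 tests |
|---|---|---|---|
| 0.3 / 0.3 | 56–57% | 68% | 81% |
| 0.5 / 0.3 | 50–52% | 58% | 73% |
| 0.5 / 0.5 | 49–50% | 58% | 70% |
| 0.7 / 0.5 | 42% | 47% | 57% |
| 0.9 / 0.8 | 27% | not run | not run |

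The 18-test column covers 23 and 33 per arm, which give nearly the same results. The other columns use 33 per arm. With zero correlation the simulation gave 59–61% for 18 tests, matching the formula.

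For a single outcome, a separate simulation with the determinants correlated 0.5 gave 12–15%, close to the 14.3% above. With two subscales the rate cannot fall below that of one subscale alone, so correlation between them moves 26.5% down towards the one-score figure, not towards 5%.

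**After the correction.** The first Holm step is 0.05/3 = 0.0167 for three tests, or 0.05/6 = 0.0083 for six. Either holds the family-wise rate at or below 5% whatever the dependence.

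**The case against.** **No stated decision rule.** The article nowhere says that one significant interaction anywhere confirms hypothesis 2. It uses the interaction to open stratified analyses, words the objective as an analysis of influence, and adds a regression. This stands: the 60% describes how often the planned tests produce at least one apparent influence, not a success criterion that the authors wrote down.

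**The size depends on correlation.** A reader might infer that the trial will probably report a spurious influence. The document does not support that in general. At 18 tests the figure falls to 42% with correlations of 0.7/0.5 and to 27% with 0.9/0.8, and the Introduction itself describes several of these constructs as related. This stands as a limit on the claim. Even 27% is more than five times the nominal 5%.

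**There is an outcome hierarchy.** The FABQ is primary and readers may treat the rest as supportive. This stands in part: it lowers the figure to about 14–26%. But the analysis section sends primary and secondary outcomes through the same test at the same level and does not confine hypothesis 2 to the FABQ.

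**An analysis plan may deal with it.** Multiplicity for secondary outcomes and effect modifiers is often left to such a document. That would answer a silence. Here the article sets a flat 5% and places a correction explicitly, at a step that does not govern the claim.

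**Power.** A reader might also infer that a single interaction test is too weak to detect a real modifier. The article gives no expected size of modification and no distribution of the determinants, so any power figure rests on invented inputs. The fix below would not raise power either. This is no part of the point.

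**Conclusion.** The point holds as a badly fixed testing rule for a stated hypothesis. At least 18 three-way interaction tests are run at 5% each, and the one correction does not cover them. With no true modification, the chance of at least one significant interaction is 60% under independence and about 40–60% under plausible assumed correlations. It is lower if the correlations are very strong and higher if subscales, pain conditions and algometry sites are analysed separately. Confined to the FABQ, it is about 14% for one score and 26% for two subscales.

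The count and the reach of the correction come directly from the article, while the correlations are assumptions. The result does not depend on which of the article's sample sizes applies. It does not show that a false claim is more likely than not.

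**What to change.** In Statistical approach, before unblinding:

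1. Limit confirmatory testing of hypothesis 2 to the primary outcome. Name one FABQ subscale and apply Holm across the time × intervention × determinant interactions for employment, education and income. If both subscales are kept, apply Holm across all six tests.
2. Close the list of determinants at these three.
3. Declare all other determinant × outcome interactions exploratory. Report them as estimates with 95% confidence intervals, and make no claim of influence from p < 0.05.

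Keeping all three determinants fits the article better than picking education alone, since the Introduction and Discussion argue for socioeconomic level as well.

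The cost is wording only, with no extra data or participants. The downside is that fewer interactions can be called significant, and the smallest confirmatory p-value must meet 0.0167 (three tests) or 0.0083 (six tests) instead of 0.05.
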